## Abstract

**Introduction:**

People with psychosis tend to have smaller social networks than both people in the general population and other people with long-term health conditions. Small social networks are associated with poor quality of life. Preliminary evidence suggests that coaching patients to increase their social contacts may be effective. In this study, we assessed whether structured social coaching improves the quality of life of patients with psychosis (primary outcome) compared with an active control group, receiving information on local social activities.

**Methods and analysis:**

A structured social coaching intervention was developed based on the literature and refined through stakeholder involvement. It draws on principles from motivational interviewing, solution focused therapy and structured information giving. It is provided over a 6-month period and can be delivered by a range of different mental health professionals. Its effectiveness and cost-effectiveness are assessed in a randomised controlled trial, compared with an active control group, in which participants are given an information booklet on local social activities. Participants are aged 18 or over, have a primary diagnosis of a psychotic disorder (International Classification of Disease: F20–29) and capacity to provide informed consent. Participants are assessed at baseline and at 6, 12 and 18 months after individual randomisation. The primary outcome is quality of life at 6 months (Manchester Short Assessment of Quality of Life). We hypothesise that the effects on quality of life are mediated by an increase in social contacts. Secondary outcomes are symptoms, social situation and time spent in social activities. Costs and cost-effectiveness analyses will consider service use and health-related quality of life.

**Ethics and dissemination:**

National Health Service REC London Hampstead (19/LO/0088) provided a favourable opinion. Findings will be disseminated through a website, social media, scientific papers and user-friendly reports, in collaboration with a lived experience advisory panel.

**Trial registration number:**

ISRCTN15815862.

Strengths and limitations of this studyBroad inclusion criteria, allowing inclusion of patients with a range of individual characteristics (eg, varying level of financial difficulties, and different types and levels of symptoms).Inclusion of a large number of urban, semiurban and rural sites, as different geographical contexts may influence the availability or convenience of social activities.Active control condition, that is, the provision of comprehensive information on local social activities.During this trial, we focused on people of working age (18–65) and only included people who are fluent in English.Since social coaching was not part of routine care before this trial, the coaches in the experimental intervention are—although trained—not experienced in this type of approach.

## Introduction

At any given time, more than 200 000 people experience a psychotic disorder in England alone. The total costs for England was estimated to be £4 billion in 2007 and £6.5 billion by 2026.^1^ People with psychotic disorders have much smaller social network sizes compared with the general population, and compared with other groups with long-term mental and physical health problems.^2 3^ Social isolation is not only a serious problem in itself, but is also linked with poor quality of life and a range of unfavourable health outcomes.^3–6^

Traditionally, pharmacological and psychological treatments have attempted to reduce the social isolation of patients with psychosis indirectly; through treating symptoms or by teaching social skills.^7^ However, the symptoms of psychosis which are mostly linked with social isolation, that is the ‘negative symptoms’ do not show a substantial response to established pharmacological treatments.^8^ Social skills training has been found to be effective in teaching these skills to patients, however, this does not translate to improved social functioning.^9^ Given the evidence that its benefits are limited, social skills training is not recommended by National Institute for Health and Care Excellence (NICE) guidelines.^4^

A systematic review by Anderson *et al*^7^ found that interventions which directly focused on supporting socialisation activities had a positive effect on reducing social isolation.^10–13^ These interventions were diverse, including guided peer support, social coaching and dog-assisted integrative psychological therapy. The largest and highest quality trial among the ones identified tested a social coaching intervention, which was the only intervention clearly targeting social contacts outside of services.^11^ This led to the decision that this model would inform our intervention development. One of the limitations identified by the systematic review was that none of the studies reported an economic analysis of the costs and benefits of the interventions.^7^

In a research programme funded by the National Institute for Health Research (https://scene.elft.nhs.uk), we developed a manualised and structured social coaching intervention. The effective components identified in the international literature^7^ were refined and adapted to the English National Health Service (NHS) context. The intervention was designed to improve patients’ quality of life through increasing their social networks.

## Objectives

### Primary objective

To assess whether the structured social coaching intervention improves the quality of life of patients with psychosis (primary outcome) compared with an active control group, which received information on local social activities.

### Secondary objectives

To understand whether changes in quality of life are mediated by an increase in social contacts (in the previous week).To evaluate whether the intervention improves secondary outcomes such as social contacts, symptoms, social situation, feelings of loneliness, time spent in social activities, health-related quality of life and whether it reduces service use.To assess costs and cost-effectiveness of the intervention.To explore implementation of the intervention.

## Methods

### Study design

Individually randomised, parallel group controlled trial. The intervention and control condition are provided in addition to standard care.

#### Eligibility criteria

##### Inclusion criteria

Patients:

18–65 years old.Diagnosis of psychosis-related condition (International Classification of Disease 10th revision, F20–29).Capacity to provide informed consent.Ability to communicate in English.Limited social network size (three or less social contacts with non-first degree relatives in the previous week).Low quality of life (score 5 or less on the Manchester Short Assessment of Quality of Life (MANSA) quality of life assessment).Not receiving hospital treatment at the time of recruitment.

Social coaches:

Mental health professionals with experience of providing mental healthcare (eg, psychiatrists, clinical psychologists, nursing staff, occupational therapists), minimum NHS Band 4 or equivalent experience.Aged 18 and over.Capacity to provide informed consent.Ability to communicate in English.

### Intervention development

The intervention developed by Terzian *et al*^11^ was taken as the starting point for the intervention tested in this trial. It was specified and expanded using approaches from solution-focused therapy and motivational interviewing, and considering previous experiences of the group in developing and evaluating complex psychosocial interventions, in particular DIALOG+.^14^ It was further modified and then manualised by the Programme Management group, which included experts in psychiatry, psychology, social work, occupational therapy, social sciences and behavioural change and experts by experience. The intervention was finalised in consultation with stakeholders.^15^ The intervention is considered to be generic and not profession-specific, so that it can be delivered by different professional groups. The role of the social coach is intended to be independent of other treatment and solely focused on the task of expanding social networks. Social coaches are not meant to establish a wider or longer-term therapeutic relationship, which might interfere with other therapeutic relationships of the patients. The theoretical framework used is shown in figure 1.

**Figure 1 F1:**
[figure not shown]
Theoretical model of intervention processes.

### Randomisation procedures

Patients are individually randomised to either the intervention or control group. The allocation ratio is 1:1. Randomisation is stratified by site (NHS Trust), ensuring balanced numbers of patients in each group at each NHS Trust. Permuted blocked randomisation with block sizes of m=6, 4 and 2 are used within each stratum. Patients are allocated to clinicians based on locality and availability that is, not randomly. The randomisation is carried out remotely by the Pragmatic Clinical Trials Unit at Queen Mary, University of London, which is also responsible for database development and assists the team with data monitoring.

### Trial arms

#### Arm 1: intervention

##### Who delivers the intervention

The intervention is delivered by clinicians from different backgrounds (eg, psychologists/assistant psychologists, social workers, nursing staff, occupational therapists and medical doctors), with a minimum level of experience and seniority equivalent to an NHS band 4. They take up a role of ‘social coach’ for the treated patient box 2.

Box 2SCENE Social coaching intervention: the eight step approachHow are the steps covered during the sessions?There is some flexibility as to how much time each step takes and to what extent they are covered within the monthly sessions varies.Session 1: Usually, the first meeting would end with steps 5 or 6.Session 2: After the second meeting an activity is agreed upon. However, it is allowed that patients and professional leave the decision to a third session or take it during the first session if this is possible.Session 3–6 (follow-up sessions): During follow-up sessions, social coach and patient discuss to what extent the activity has been done. The social coach provides positive feedback and—if required—deals with complete or partial perceived failure using solution focused techniques (eg, emphasising what went well).After 3 months (ie, session 3–4), the situation is re-evaluated. If the activity is working well, then this is monitored in further follow-up sessions. In case professional and patient come to the conclusion that the originally planned activity does not work, a face-to-face meeting is arranged in which steps 4–8 of the initial meetings are repeated and a different activity is planned.

##### Type and frequency of sessions

Social coaches meet patients at least three times but ideally monthly over the 6-month intervention period. During the first two sessions of the intervention, a structured eight step approach is followed and then revisited in follow-up meetings. Please see details of the eight step approach and of the intervention sessions in box 2.

The intervention starts with two initial face-to-face sessions (which can also occur via video conferencing), each lasting between 60 and 90 min. The main aim of these initial meetings is to introduce the intervention, explore participants’ social history and discuss preferences and options for activities. The participant then selects one social activity to focus on during the remaining meetings and actions are agreed. The subsequent meetings include discussions around challenges and progress and and take place monthly, lasting about 20 min each. The final meeting is face-to-face and is used as both a summary of progress and to plan for future social activities after the intervention. The intervention can be stopped at any time on participant request.

##### Training and supervision of social coaches

Social coaches are trained in one session lasting 3 hours, normally in a group format (although one-to-one sessions can be arranged). Training is provided by senior SCENE researchers.

During the training coaches acquire knowledge of the structure and aims of the intervention, and of simple motivational interviewing (eg, identifying change talk) and solution focused therapy techniques (eg, identifying what has worked in the past). Scenarios in which barriers for the patients in engaging in new social activities may appear and strategies to overcome them are discussed.

Learning progress is assessed during the training and in the subsequent supervision, provided by senior members of the research team.

Clinicians receive updates on changes in options for activities from the local research team. They will also receive at least two supervision sessions by SCENE senior researchers.

### Arm 2: control group

Patients in the control group are provided with information about local options for social activities via a booklet sent to them in the post or handed over by a researcher. This is intended to control for the provision of information on social activities and service attention to their social isolation.

### Outcomes

#### Primary outcome

The primary outcome is subjective quality of life, measured with the MANSA at the end of the intervention period (6 months after randomisation).

The MANSA has been widely used in research and cited in more than 850 research papers. The MANSA is brief with very high completion rates and excellent psychometric properties.^16^

### Mediator of effect on primary outcome

Number of social contacts in the previous week, measured at 6 months follow-up using the Social Contacts Assessment (SCA).^17 18^

### Secondary outcomes

Social Contacts (SCA).^17^Psychopathological symptoms assessed with the Positive And Negative Syndrome Scale.^19^Social situation with the SIX.^20^Feeling of loneliness with the University of California, Los Angeles (UCLA) Loneliness Scale.^21^Time spent in social activities with the Time Use Survey.^22^Health-related quality of life with the EQ-5D-5L.^23^Service use with the Client Service Receipt Inventory,^24^ and from NHS Digital datasets.^25^

Study outcomes and timepoints are summarised in table 1.

**Table 1 T1:** Scene study outcomes and time points

Assessment	Screening	Baseline	Study phase (6 months)	Follow-up (12 months)	Follow-up (18 months)
All patient participants					
MANSA	x	x	x	x	x
Social contacts assessment	x	x	x	x	x
PANSS		x	x	x	x
Social situation		x	x	x	x
Loneliness		x	x	x	x
Time spent in social activities		x	x	x	x
EQ-5D-5L		x	x	x	x
Client service receipt inventory		x	x	x	x
Healthcare source use (NHS digital)		x	x	x	x
Intervention participants only					
Semistructured interviews			x		
Social coaches					
Adherence schedule			x		
Semistructured interviews			x		

MANSA, Manchester Short Assessment of Quality of Life; NHS, National Health Service; PANSS, Positive And Negative Syndrome Scale.

### Patient and public involvement

A Lived Experience Advisory Panel (LEAP) has been set up and meets every 6 months to advise on study progress, review materials and support dissemination plans.

The LEAP has a central role in the preparation of study materials, design of practical procedures and dissemination. For example, LEAP members provided valuable feedback during the development of the intervention, and for facilitating recruitment and finding out about available activities in the community. The chair of the LEAP is an expert by experience who attends regular meetings with the project team and is directly involved in parts of the research, in particular the interpretation of qualitative data. Findings from all work packages, including the intervention development are discussed with and influenced by the LEAP.

### Internal pilot

The trial comprised an internal pilot with the aim of checking the feasibility of recruiting to target. The recruitment target for the internal pilot was 140 participants representing an average rate of four participants per site per month for 5 months. This was achieved within the 5-month time frame.

### Independent committees

The trial has an independent project steering committee and a data monitoring committee. Both include among their members one clinician/clinical researcher, one quantitative methodologist and one person with lived experience of mental illness.

### Analyses

#### Statistical analysis

The primary outcome analysis will be the comparison of mean MANSA scores between treatment groups at 6 months follow-up using a heteroscedastic partially nested mixed-effects model.^26^ This model will account for clustering by treating clinician in the intervention arm, baseline values of the outcome (MANSA) and site as covariates.

Secondary outcomes will be analysed using the same model as for the primary outcome or an equivalent model appropriate for the outcome type where the secondary outcome is not continuous. Differences in outcome measures between groups will be compared for 6 months, 12 months and 18 months follow-up data. Additionally, repeated measures models comprising all four time points will be fitted. Baseline characteristics of patients will be tabulated by treatment arms.

The analysis will be on an intention-to-treat basis, and every effort will be made to collect complete data. If any outcome data are missing, available subject data only will be analysed (unbiased analysis under missing-at-random assumption); however, patterns of missing data will be explored, and a strategy for dealing with missing values will be articulated in the formal statistical analysis plan.

We are planning individual level single imputations (replacing missing values by a fixed value defined by a certain rule) analyses for partially completed primary outcome data to assess the uncertainty around the primary outcome analysis estimate. Further details of other sensitivity analyses planned will be outlined in the statistical analysis plan prior to analysis.

A mediator analysis will identify whether the effect on the primary outcome is mediated through expanded social networks (SCA) at 6 months, as hypothesised. The product of coefficients method, with a Sobel test and bootstrap standard errors will be used.^27^ Further mediation analyses will assess the mediation effect of increases in SCA at 6 months on patients’ MANSA score at 12 months follow-up.

All analyses are incorporated into a statistical analysis plan, and allocation codes will not be released to the statistician before the analysis plan is signed off. All researchers involved in developing the analysis plan will remain blinded until the analysis plan is signed off.

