### Sample size calculation

It is assumed that the proposed new intervention would be implemented and funded across the NHS only if it achieved at least a medium sized effect. An effect size of 0.35 is equivalent to an improvement of satisfaction ratings on the MANSA of at least one scale point (on a 7-point scale) for 4 out of a total of 12 life domains. An improvement of quality of life in four life domains is usually regarded as a meaningful difference to patients’ life.^16^

For detecting such an effect size with 90% power, assuming a conservative intraclass correlation coefficient (ICC) of 0.07 for patients treated by the same professional in the intervention group, 229 patients in the intervention group and 229 in the control group will be required (total sample=458). A 1:1 allocation ratio has been chosen for organisational ease. This requires eight additional patients to be recruited compared with the absolute minimum required sample size with slightly uneven groups. A drop-out rate (from the study) at 6 months follow-up of 20% (in line with recent trials of similar interventions with the same patient group) (VOLUME trial) was assumed.^18^ The sample size calculation was based on 10 patients being treated and followed-up per clinician on average. Based on recruiting 12 patients per clinician the final total sample size target was 576 patients (288 per arm). Recruitment and intervention delivery to SCENE were paused during the COVID-19 pandemic making a study extension necessary (see the section Impact of the COVID-19 pandemic). For this a sample size recalculation was conducted using values observed so far for two quantities. The drop-out rate was inflated from 20% to 25% (actual rate to date 24%). Cluster size in the intervention arm was reduced from 10 to 3 patients per treating professional on average allowing for observed variability in patients per professional. Using these estimates the updated total number of patients to recruit is 504.

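### Table 1 schedules MANSA at screening and at baseline, but the primary model adjusts only for the baseline value; if these are separate assessments, adding the screening score is a small, nearly free gain in precision

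*Protocol article*

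**What the plan says.** - **Primary model.** Under Statistical analysis, 6-month MANSA is compared between arms with a partially nested mixed model that allows for clustering by clinician in the intervention arm, with "baseline values of the outcome (MANSA) and site as covariates". The screening score is not named.
- **Schedule.** The header of Table 1 (Secondary outcomes) begins "Assessment Screening Baseline Study phase (6 months", so screening and baseline are separate columns. MANSA and the Social Contacts Assessment are marked in both. Every other patient measure starts at baseline.
- **Why MANSA is taken at screening.** It is an entry criterion: "Low quality of life (score 5 or less on the Manchester Short Assessment of Quality of Life (MANSA) quality of life assessment".
- **Repeated-measures models.** The same section says "repeated measures models comprising all four time points will be fitted". The abstract lists the assessments: "Participants are assessed at baseline and at 6, 12 and 18 months after individual randomisation". Together these give baseline, 6, 12 and 18 months, so screening is not counted there either.

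The article does not say whether the two early MANSA marks are two administrations, how far apart they are, or how strongly they correlate with each other or with the 6-month score.

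**The concern.** If the two marks in Table 1 are two administrations, the trial holds two pre-randomisation readings of its primary outcome and the stated model uses one. MANSA, like any rating, varies from one occasion to the next. Two readings therefore usually predict the 6-month score somewhat better than one, and a better prediction lowers the residual variance of the treatment comparison. Because the screening score precedes randomisation, adjusting for it cannot bias the treatment effect.

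What is at stake is a slightly narrower confidence interval from data already collected. The validity of the primary result is not in question.

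**Working it through.** **1. Does the planned sample size depend on this?** The Sample size calculation section gives a standardised effect of 0.35 ("An effect size of 0.35 is equivalent to an improvement of satisfaction ratings on the MANSA of at least one scale point"), the power ("For detecting such an effect size with 90% power") and the clustering ("assuming a conservative intraclass correlation coefficient (ICC) of 0.07 for patients treated by the same professional in the intervention group"). It gives no significance level, so two-sided 5% is assumed here. With m patients per clinician in one arm only,

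n per arm = (1.960 + 1.282)² × [1 + 1 + (m − 1) × 0.07] / 0.35².

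- Before the pandemic, m = 10: 10.507 × 2.63 / 0.1225 = 225.6, so 226 per arm and 452 in total. The article states 229 and 458, which is 1.3% away.
- Revised, m = 3, equal clusters: 10.507 × 2.14 / 0.1225 = 183.6, so 184 per arm, or 492 to recruit after 25% drop-out. The article states 504, which is 2.4% away.
- Revised, allowing for unequal clusters with an assumed coefficient of variation of 0.5: m becomes 3 × 1.25 = 3.75, n = 10.507 × 2.1925 / 0.1225 = 188.1, so 189 per arm, 378 analysable, and 378 / 0.75 = 504.

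The stated figures are reproduced to within rounding and method. No correlation with baseline enters them, so the sample size takes no credit for any covariate and does not change with this point.

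**2. Gain without the entry cut.** Let r be the correlation of each early reading with the 6-month score, and b the correlation between the two early readings. Both are assumed.

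- Residual variance with one reading: 1 − r².
- With two readings: 1 − 2r²/(1 + b).

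For r = 0.5 and b = 0.7 these are 0.750 and 1 − 0.5/1.7 = 0.706, a fall of 5.9%. For r = 0.3 and b = 0.9 they are 0.910 and 0.905, a fall of 0.5%. For r = 0.6 and b = 0.7 they are 0.640 and 0.576, a fall of 9.9%.

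**3. Gain with the entry cut.** Admitting only people at or below 5 at screening narrows the spread of the screening score and so reduces what it can add. Take scores as normal with an assumed mean of 4.5 and SD of 0.95.

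- The cut lies at c = (5 − 4.5)/0.95 = 0.526 SD, which admits 70%.
- With λ = φ(c)/Φ(c) = 0.496, the screening variance shrinks to v = 1 − cλ − λ² = 0.493 of its uncut value, so 1 − v = 0.507.
- For r = 0.5 and b = 0.7, among those admitted: baseline variance = 1 − 0.49 × 0.507 = 0.752; 6-month variance = 1 − 0.25 × 0.507 = 0.873; their covariance = 0.5 − 0.35 × 0.507 = 0.323.
- Residual variance given baseline alone: 0.873 − 0.323²/0.752 = 0.735. Given both readings it stays 0.706, because selecting on a covariate does not change the variance conditional on it.
- Fall: 1 − 0.706/0.735 = 3.9%, or 2.0% of the standard error.

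The same steps over assumed means of 4.2 to 4.8 give this percentage fall in residual variance against baseline alone:

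| r | b = 0.7 | b = 0.8 | b = 0.9 |
|---|---|---|---|
| 0.3 | 1.0 to 1.3 | 0.7 to 0.9 | 0.4 to 0.5 |
| 0.4 | 2.0 to 2.5 | 1.4 to 1.7 | 0.8 to 0.9 |
| 0.5 | 3.5 to 4.4 | 2.5 to 3.0 | 1.4 to 1.6 |
| 0.6 | 6.0 to 7.5 | 4.2 to 5.0 | 2.3 to 2.6 |

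In round terms this is 0.5% to 7% of residual variance, and about 0.2% to 4% of the standard error. Against 378 analysable patients, that range is worth about 0.005 × 378 = 2 to 0.07 × 378 = 26 patients. The conversion is generous, since it treats the whole error as patient-level and ignores the clinician component.

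**4. If one administration fills both columns,** b = 1. The two-reading formula becomes 1 − r², the gain is zero, and two identical covariates cannot both be estimated.

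**The case against.** The strongest reply is that nothing here is wrong. Adjusting the 6-month score for its baseline value and for the stratification factor is a standard, unbiased analysis, and a second precision covariate is a matter of preference. Table 1 marks two columns but nowhere says that MANSA is given twice. The abstract's list of assessments and the count of four time points fit a single pre-randomisation reading as well as two. Every correlation used above is assumed, and at the low end the gain is negligible. The statistical analysis plan, which is not shown, may already settle the matter.

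Most of this stands, and it is why the point is conditional and minor. What remains is that the article does state the covariate set and, on the plain reading of Table 1, leaves out a scheduled pre-randomisation measure of the primary outcome.

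A reader might infer more than the article supports:

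- *That it is unclear which reading serves as baseline.* The model names the baseline value and Table 1 separates the columns. Nothing suggests the screening score would be used in its place.
- *That people scoring above 5 at baseline after qualifying at screening might be excluded.* No such exclusion is proposed, and the analysis is by intention to treat.
- *That the same gain applies to social contacts.* That measure is a count limited to three at entry, and the normal-theory working above does not carry over to it.
- *That the trial is underpowered because of this.* Step 1 of the working shows that it is not.

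**Conclusion.** The point holds as a small, optional improvement. The planned model is valid and unbiased, and the target of 504 is unaffected. If screening and baseline MANSA are separate administrations, using both would lower residual variance by about 0.5% to 7% against baseline alone, or the standard error by about 0.2% to 4%. This rests on assumed correlations (0.3 to 0.6 with the 6-month score, 0.7 to 0.9 between the early readings), roughly normal scores, and entry cut at a screening score of 5. If one administration fills both columns, there is no gain and nothing to change. To say that the screening score is wasted, or that adding it is certain to sharpen the estimate, goes further than the article allows.

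**What to change.** Before unblinding, confirm from the trial procedures whether screening and baseline MANSA are separate administrations.

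- **If they are:** add screening MANSA as a second covariate in the primary model, keeping baseline MANSA and site, or replace the single baseline value by the mean of the two readings. Record the choice in the statistical analysis plan. The article says that allocation codes are withheld until that plan is signed off, so the choice can be made blind.
- **If they are not:** keep the stated model and do not enter the second covariate.

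The cost is one degree of freedom among several hundred patients (none if the mean is used) and no new data collection.
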